### Objectives

This paper is the first of its kind to describe a transparent, uniform methodological design for the economic evaluation of several different trial-based interventions in the field of employability, disability and return-to-work. Known as the 'CASE-study' (Cost-effectiveness Analysis of Sustainable Employability), the project's aim is to evaluate at least five different employability interventions. All of the interventions share the common aim of reducing absenteeism and optimising the employability of employees with a known disability or those at risk of disability due to musculoskeletal complaints, mental health problems or a combination of both musculoskeletal and mental health complaints. In contrast with previous studies, the project design has no population restrictions and allows for the economic evaluation of any employability intervention regardless of the population they were developed for. Furthermore, the project also includes interventions provided in the primary and specialist health sectors as well as those delivered within the workplace. It also includes interventions aimed at reducing health care costs, wage replacement costs and other intervention costs in addition to improvements in return to disability duration and work return rates as measured by self-reported return to work dates, total duration of absence and subsequent recurrences, etc. Other outcomes include quality of life, quality of work life and general health status, etc. In addition, we cast a wide net to include a range of study designs since RCTs are not always possible in the economic evaluation of employability interventions. This paper describes the patient inflow in the event of an RCT or a quasi-experiment with a matched controlled design being conducted. For every employability intervention, an effect study will be conducted. In addition, from a societal perspective, a trial-based economic evaluation for every employability intervention will be carried out in a consistent manner. The results of these analyses will be discussed elsewhere in the future, but we hypothesize that the employability intervention is preferable in terms of costs, effects and utility compared to usual care. This paper will therefore demonstrate the strength of the CASE-study project in prescribing a methodological design which allows for the assessment of several different types of employability interventions within varying populations.

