
**Figure 1 F1:**
[figure not shown]
**Employability interventions included in the CASE-study**.

It is beyond the scope of this design article to describe the precise content of each employability intervention in detail. This will be done when the results of the economic evaluation per employability intervention are published. What is of importance in this paper is that the employability interventions use an innovative, systematic approach in order to support work participation in employees with health complaints. These are innovative because both the healthcare system and the private/work life of the employees are considered in the intervention. The features of the interventions differ according to the patient population, but the aim remains the same: to reduce sickness absence and increase the potential of achieving sustainable employability.

The protocol for this study has been approved by the Ethics Committee of Psychology (ECP107) at Maastricht University, the Netherlands.

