### Effect evaluation

#### Primary outcome measure

The primary outcome measure in the CASE-study is reduced sickness absence duration in calendar days. Reduced sickness absence will be measured subjectively via patient self-report records. The duration of sick leave will be calculated as the time in calendar days since reduced productivity occurred (baseline). This will then be compared with the productivity time of a person at 6, 12, and 18 months. The success of an intervention will be defined by comparing the average reduction in sickness absence between the intervention group and the control group. The employability intervention is effective when the employees in the intervention group return to work twice as quickly as employees in the control group. Data on sickness absence duration will be gathered by using the productivity and disease questionnaire (PRODISQ) [45].

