### Data analyses

#### Effectiveness

All statistical analyses, performed to distinguish differences between the control group and the intervention group, will be performed according to the intention-to-treat principle. This means that the participants will remain in the group they were allocated to at baseline. All data regarding primary and secondary outcomes will be analysed using descriptive statistics. To control for protocol deviations likely to cause bias, data will be analyzed using per-protocol analyses whereby outcomes will be compared between those participants who received at least one or a partial intervention session and the control group. With the aim of correcting for possible regression to the mean, the baseline value of the particular outcome variable will be added to the model. Days of sick leave in the year before the inclusion, measured at baseline, will be added as a potential effect-modifier.

Diagnosis and prognostic parameters can be confounders, thus the Cox regression analysis for confounders will be used to adjust for differences between control and intervention groups. If necessary, differences in baseline will be adjusted for prognostic dissimilarities. Missing data will be handled using SPSS missing value analysis on item level. Completely missing measurements will be handled using multiple imputation.

The primary dependent variable is days of absence from work. In order to estimate the number of absence days, survival analyses will be used. There are two reasons why we opted to use survival statistics. Firstly, the time to sustainable employability is unlikely to be normally distributed which will make parametric statistical analysis difficult or inappropriate. Increasing productivity can occur quite early, possibly within months, but can also, as expected in the care as usual situation, may not be prolonged or may even decrease again. Secondly, survival analysis accounts for dropout by the technique of censoring. Participants who drop out will have the same hazard of sustainable employment than those that remained in the study. The Cox Proportional hazard model will therefore be used to analyse the HR of the days of sick leave duration. Reduced sickness absence duration in calendar days will be analysed with the Kaplan Meier survival method, and the differences in absence duration between both groups will be tested with a log rank test.

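### The primary outcome is days of sickness absence, but the primary analysis is a single-event survival analysis that does not estimate total days when absence recurs, and its event is named inconsistently

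*Protocol article*

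**What the plan says.** The Primary outcome measure section defines the outcome as a quantity of days: "The primary outcome measure in the CASE-study is reduced sickness absence duration in calendar days". It then gives two yardsticks. The first is a mean: "The success of an intervention will be defined by comparing the average reduction in sickness absence between the intervention group and the control group". The second is a speed: "The employability intervention is effective when the employees in the intervention group return to work twice as quickly as employees in the control group". The second does not require the return to last.

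The Effectiveness part of Data analyses again names days of absence as the primary dependent variable and continues: "In order to estimate the number of absence days, survival analyses will be used". The methods are Kaplan-Meier curves, a log-rank test and a Cox model. In justifying them, the section refers to time to sustainable employability and, on censoring, to the hazard of sustainable employment. It also says that gains in productivity "may not be prolonged or may even decrease again", and it attaches that expectation to care as usual.

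Recurrence appears in two other places. The Objectives list "total duration of absence and subsequent recurrences" among the measures. The secondary outcome Sustainable employability calls an intervention unsuccessful if more than fourteen consecutive days of absence follow it. The general aim of the interventions is "to reduce sickness absence and increase the potential of achieving sustainable employability".

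**The concern.** A mean difference in absence days and a hazard ratio for one event answer the same question only if absence does not come back once the event has occurred. Here the protocol says that it may. Days lost after the event do not enter a Kaplan-Meier, log-rank or Cox analysis of that event, so the analysis as described does not deliver the number of absence days.

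The event itself is also unsettled. If it is return to work, a short-lived return ends the clock. If it is sustainable employment, it may not. The two readings can give different hazard ratios from the same data. The studies are unblinded and one design serves five interventions, so the choice should not be left open until the data are seen.

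Two consequences follow. The primary conclusion may misstate the quantity the protocol calls primary. It may also disagree with the economic evaluation, which costs the number of days of sickness absence.

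**Working it through.** **1. What the plan's own figures rest on.** The Sample size section uses a hazard ratio of 2.0, 80% power and a 0.05 level. By Schoenfeld's formula (two-sided, 1:1), the number of events is 4 × (1.960 + 0.842)² / (ln 2)² = 65.3, so 66. The stated 120 employees then imply an event fraction of 66/120 = 55%, which the article does not give. Allowing for 15% dropout, 120/0.85 = 141.2, so 142, as stated. The size is thus consistent with a time-to-one-event analysis. The same section nevertheless reads the hazard ratio of 2.0 as a relevant difference in average hours or days lost.

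**2. Illustrative model (assumptions, not in the documents).** Time to first return is exponential with median 60 days (intervention) and 120 days (control), so the first-return hazard ratio is exactly 2.0. The horizon is 547 days (18 months). A proportion p of each arm relapses once, starting a mean of 60 days after return, with a mean spell of 120 or 180 days. Everything is cut off at day 547.

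**3. Absence up to first return.** The mean is (1/h)(1 − e^(−547h)), with h = ln 2/median.
- Intervention: 86.6 × (1 − 0.0018) = 86.4 days
- Control: 173.1 × (1 − 0.0424) = 165.8 days
- Difference: 165.8 − 86.4 = 79.4 days

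**4. Days added by a relapse.** By simulation (4 million per arm), a relapser adds on average, within the horizon:
- mean spell 120 days: 112.9 (intervention), 100.3 (control)
- mean spell 180 days: 156.1 (intervention), 135.9 (control)

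The intervention figure is larger because earlier returners have more follow-up left. The saving for 120-day spells is therefore 79.4 + 100.3 × p(control) − 112.9 × p(intervention).

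| Relapse, intervention vs control | Mean spell | Saving in total days |
|---|---|---|
| none | – | 79 |
| 20% vs 20% | 120 | 77 |
| 40% vs 40% | 120 | 74 |
| 40% vs 20% | 120 | 54 |
| 60% vs 20% | 120 | 32 |
| 60% vs 20% | 180 | 13 |
| 20% vs 40% | 120 | 97 |
| 20% vs 60% | 120 | 117 |

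The first-return hazard ratio is 2.0 in every row.

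**5. When the saving disappears.** With control relapse at 20%, the intervention relapse that brings the saving to zero is (79.4 + 0.2 × 100.3)/112.9 = 88% for 120-day spells, and (79.4 + 0.2 × 135.9)/156.1 = 68% for 180-day spells. A second model allowed repeated spells over 548 days, with later spells ending at the control rate. With 43% of controls returning by 18 months, total absence is 432 days (control, relapse 20% per year) against 431 (intervention, 80% per year). With relapse of 20% per year in both arms it is 432 against 352, a saving of about 80 days.

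**6. The opposite error.** Suppose both arms return equally fast (first-return hazard ratio 1.0) and 60% of controls but 20% of the intervention arm relapse. With a median return of 60 days in both arms, the true saving is 0.4 × 112.9 = 45 days for 120-day spells and 0.4 × 156.1 = 62 days for 180-day spells. A first-return analysis would show none of it.

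**The case against.** A reader might infer that the analysis stops at the first return to work, and that an intervention producing quick but short-lived returns would meet the primary goal without reducing absence. The documents do not support that reading.
- No section says the clock stops at the first return. The analysis section speaks of sustainable employability and employment, under which a brief return need not count.
- The protocol expects non-lasting gains under usual care. If such returns counted as events, the benefit of the intervention would be understated.
- Every scenario in the table still shows a saving. Removing it takes far more relapse under the intervention than under control, and nothing in the documents suggests such an excess.

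It can also be said that an article leaves event coding to the full protocol or analysis plan, and that relapse would show up elsewhere, in the sustainability outcome at 12 and 18 months and in the costed absence days.

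These points rule out a claim of bias in one direction. They do not remove the mismatch. The article itself states days as the outcome, a single-event method to estimate them, and two different events. That is a conflict in what is written, not a detail left out. The sustainability rule is secondary, is not tied to the primary event, and is worded in terms of having received the intervention, so it does not transfer to controls as it stands.

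**Conclusion.** The point holds in this form: the primary quantity is average absence days, the only primary methods describe time to one event, and that event is return to work in one section and sustainable employment in another. Where absence recurs, the hazard ratio does not determine the reduction in days and can err either way. At a fixed first-return hazard ratio of 2.0, the saving ranged from 13 to 117 days across the relapse patterns tried, against 79 with no relapse. With equal relapse in both arms it hardly moved (74 to 77 days for 120-day spells). The size therefore depends on a difference in relapse between arms. The relapse rates, spell lengths and return times are all assumptions. The mismatch between outcome and method does not depend on them.

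**What to change.** In the Primary outcome measure and Effectiveness sections, name the between-group difference in total absence days over 0 to 18 months, all spells included, as the quantity that answers the average-reduction question. Give it a confidence interval, for example by the non-parametric bootstrap already planned for costs, and report it with the hazard ratio.

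For the hazard ratio, use one event definition in the Primary outcome measure, Sustainable employability and Effectiveness sections. State whether the fourteen-day rule applies and, if so, over what fixed window after return, identically in both arms. The window matters. Without one, an unrelated absence late in follow-up could cancel an early return, early returners would be exposed to disqualification for longer, and people who drop out after returning could not be classified.

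The cost is one added analysis, using absence days that the economic evaluation already needs, and slightly fewer events if a durability condition is adopted.

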**Methods/design:**

Per employability intervention 142 participants are needed whereof approximately 66 participants receiving the intervention will be compared with 66 participants receiving usual care. Based on the intervention-specific characteristics, a randomized control trial or a quasi-experiment with match-criteria will be conducted. Notwithstanding the study design, eligible participants will be employees aged 18 to 63, working at least 12 h per week, and at risk of work disability, or already work-disabled due to medical restrictions. The primary outcome will be the duration of sick leave. Secondary outcomes are health status and quality of life. Outcomes will be assessed at baseline and then 6, 12 and 18 months later. Economic costs will consist of healthcare costs and cost of lost production due to work disability, and will be evaluated from a societal perspective.

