#### Randomization/matching

In the case of randomization, the minimization method will be applied. Minimization aims to ensure an excellent balance for several prognostic factors in small groups [40]. Employees consenting to participate will be pre-stratified according to age (18-32 years, 33-48 years, 49-64 years), gender, and working hours (12-24 h/week, > 24 h/week). Since health care providers will treat participants in both the intervention and in the control groups, the study cannot be blinded. Matching i.e. formulating experimental and control groups on the basis of pairing participants on the basis of predetermined matching criteria will be used. These matched-criteria are age, working hours and health complaints. Thus, an employee in the intervention group will be matched to someone meeting the same criteria who will then act as a member of the control group.

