### Economic evaluation

The economic evaluation will be carried out according to the intention-to-treat principle. Non-parametric bootstrapping (1000 replications) will be used to obtain 95% confidence intervals to estimate the uncertainty surrounding the cost differences, because cost-data are usually skewed to the right [57].

For the cost-effectiveness analysis, the incremental cost-effectiveness ratio (ICER) will be calculated by assessing the ratio of the differences in costs between the groups to the differences in effects between the groups. The ICER indicates whether the additional investments needed for the interventions gain at least one extra unit of effect compared with care as usual [57]. The cost-utility ratio will be calculated by the incremental costs divided by the difference in QALYs [39,58].

Bootstrapping with 5000 replications will be used to estimate the sample-uncertainty around the point estimates (ICER and ICUR). The bootstrapped ICERs and ICURs will be graphically presented on a cost-effectiveness plane. Furthermore, acceptability curves will show the probability that the employability intervention is cost-effective at a specific ceiling ratio, which is the maximum amount of money society is willing to pay to gain one extra unit of effect or a gain in quality of life [59]. Finally, the robustness of the different parameters on the cost-effectiveness calculation will be assessed by sensitivity analyses. Data processing will be done in SPSS 17.0 and bootstrapping will be carried out in Excel.

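### In the matched quasi-experiments the primary log-rank test ignores the matching, and the Cox adjustment rule does not ensure that the matching factors enter the model, so the comparison may be conservative

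*Protocol article*

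**What the plan says.** The abstract of the protocol article allows two designs: for each intervention, "a randomized control trial or a quasi-experiment with match-criteria will be conducted". The section Randomization/matching assigns minimization to the randomised evaluations. For the others it describes forming "experimental and control groups on the basis of pairing participants on the basis of predetermined matching criteria", so that each intervention employee "will be matched to someone meeting the same criteria who will then act as a member of the control group". It then lists the factors: "These matched-criteria are age, working hours and health complaints".

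The Effectiveness part of Data analyses gives one primary analysis for both designs. Kaplan-Meier curves are drawn and "the differences in absence duration between both groups will be tested with a log rank test". In addition, "The Cox Proportional hazard model will therefore be used to analyse the HR of the days of sick leave duration". Neither method is given a pair term, a stratum or a clustered variance. The same section treats diagnosis and prognostic parameters as possible confounders. It uses Cox regression to adjust for differences between the groups, with adjustment for baseline differences only where judged needed. The baseline value of the outcome and sick leave in the previous year are also to be added.

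Sample size gives 120 employees for HR 2.0, 80% power and a 0.05 level, and 142 after 15% dropout. It does not mention matching.

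**The concern.** Two employees matched on age, working hours and health complaint will tend to have similar absence durations if those factors predict return to work. The variance of the group difference is then Var(A) + Var(B) − 2·Cov(A,B), with a positive covariance. The ordinary log-rank test and an unadjusted Cox model set the covariance to zero. Their variance is too large, their true level falls below 5%, and the HR interval from the unadjusted Cox model is too wide.

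The log-rank test as named takes no covariates, so adjustment in the Cox model cannot repair it. The Cox rule does not close the gap for certain either. It looks for differences between groups, and good matching removes such differences in exactly these three factors. An analyst could follow the rule faithfully and leave them out.

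At stake is a real benefit being reported as not shown, in studies that the article sizes at 80% power.

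**Working it through.** **The plan's own figure.** 120 / (1 − 0.15) = 141.2, rounded up to 142, as stated. For HR 2.0, a two-sided 0.05 level (sidedness is not stated, so this is assumed) and 80% power, Schoenfeld's formula for two independent groups gives 4·(1.960 + 0.842)² / (ln 2)² = 65.3, so 66 events. Then 66/120 = 55% of employees would need to have the event. The article states no event proportion, so 120 is possible but cannot be confirmed.

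**Inputs assumed.** 60 pairs (the plan's 120, 1:1), exponential times, a shared gamma frailty θ per pair with Kendall tau = θ/(θ + 2), and administrative censoring. HR 2.0 is taken within the pair. The documents give no tau, so a range is shown. Each setting has 2000 runs. Simulation standard error is about 0.5 points near 5% and 0.9 points near 80%.

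**No true effect, about 38–45% events:**

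| tau | log-rank rejection | model-based SE / empirical SE |
|---|---|---|
| 0 | 4.3% | 0.275/0.268 = 1.03 |
| 0.05 | 4.3% | 0.278/0.269 = 1.03 |
| 0.11 | 3.8% | 0.282/0.260 = 1.08 |
| 0.20 | 3.0% | 0.288/0.258 = 1.12 |
| 0.33 | 2.1% | 0.302/0.259 = 1.17 |

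The values at tau 0 and 0.05 are within simulation error of 5%. As a check, an SE too large by a factor k gives a level of P(|Z| > 1.96k): k = 1.116 gives 2.9% and k = 1.166 gives 2.2%, in line with the table. With longer follow-up (about 67–87% events over the whole range of tau), rejection falls to 2.0% at tau 0.20 and 0.9% at 0.33, with SEs 19% and 35% too large.

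**Within-pair HR 2.0, about 46–58% events, power:**

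| tau | plain log-rank | Cox, pair-robust variance | log-rank stratified by pair |
|---|---|---|---|
| 0 | 82% | 82% | 66% |
| 0.05 | 80% | 80% | 66% |
| 0.11 | 72% | 77% | 61% |
| 0.20 | 66% | 74% | 61% |
| 0.33 | 49% | 66% | 54% |

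Only the gap between the first two power columns is due to the variance. The fall down each column also reflects fewer events and an estimated effect that shrinks when a strong shared factor is left out (mean log HR 0.70 at tau 0, 0.54 at tau 0.33).

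**Putting the factor in the model.** A second simulation (1500 runs per setting, 60 pairs) made the shared effect an observed covariate with SD 0.35, 0.7 or 1.0 on the log-hazard scale. With HR 2.0, power was 82%, 73% and 60% unadjusted, and 84%, 85% and 83% adjusted. With no effect, rejection was 4.4%, 2.5% and 1.7% unadjusted, and 6.0%, 5.2% and 4.9% adjusted (simulation standard error about 0.6 points). At SD 0.7 and 1.0 the adjusted SE matched the empirical one: 0.262 against 0.262, and 0.261 against 0.263.

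**The case against.** Four points can be made on the other side.

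- **The Cox model is not planned as unadjusted.** Diagnosis is close to health complaints, and age and working hours are plausible prognostic parameters. A reader might infer that every standard error, p-value and interval of the primary analysis is wrong. The documents do not support that. If the factors are in the model, its SE is about right. A further simulation with three shared factors (log HR 0.5 per level, number of levels assumed) gave power of 71% unadjusted, 77% unadjusted with pair clustering, 81% adjusted, and 80% adjusted with clustering. Clustering therefore adds little once the factors are included. What stands is that the text does not guarantee their inclusion and that the log-rank test cannot take them.
- **Power need not fall below plan.** If HR 2.0 is the overall rather than the within-pair ratio, a copula simulation at about 54% events gives the plain log-rank 80% to 85% power for correlations from 0 to 0.5, against 79% to 94% for a pair-robust test. The loss is then only relative to the better method. The article does not say which HR is meant.
- **The size is assumed.** Three broad matching factors may induce little correlation, and at tau 0.05 there is nothing to gain. This stands.
- **Bootstrap and multilevel models.** A reader might infer that the cost and ICER/ICUR intervals are also wrong. The economic section says only that "Non-parametric bootstrapping (1000 replications) will be used to obtain 95% confidence intervals", and names no resampling unit; the multilevel models list no levels. A condensed article may leave both to the full plan, and no error is shown there.

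**Conclusion.** The point holds in a limited form. In the matched evaluations, the named log-rank test does not use the matching, and the Cox adjustment rule does not ensure that the balanced matching factors enter the model. If those factors predict return to work, the log-rank test and any Cox model without them are conservative and less powerful than they could be. Over the assumed tau of 0.05 to 0.33, the shortfall against a pair-robust Cox test is 0 to 17 percentage points of power, and the true level runs from about nominal down to 2.1% (0.9% with longer follow-up).

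These figures rest on 60 complete pairs, two-sided testing, exponential times, gamma frailty and a correlation that the documents do not give.

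A reader might also infer a risk of false positive claims. With positive within-pair correlation the error goes the other way. Any residual confounding from non-random allocation is a separate matter. The randomised evaluations are not touched, and the visible text does not say how many of the five evaluations are matched.

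**What to change.** For the matched evaluations only:

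- Make the primary test the group effect from a Cox model that always includes age, working hours and health complaint, whether or not the groups differ on them. Cluster the variance on the matched pair as a safeguard against residual correlation.
- Keep the Kaplan-Meier curves and the ordinary log-rank test as descriptive.
- Do not stratify by pair. In the frailty simulation the stratified log-rank had less power than the plain one up to tau 0.20 (66% against 82% at tau 0), and it loses pairs that have lost a member.
- For consistency, state that matched pairs are the units drawn in the cost and ICER/ICUR bootstraps.

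The cost is small: a change of wording, a pair identifier kept in the data set, and possibly software other than SPSS 17.0 for the clustered variance. No further participants or measurements are needed. With no within-pair correlation, the pair-robust Cox test gave up no power (82% for both tests).
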